### Sample size considerations

From our systematic reviews [17], 20% of women with early-onset pre-eclampsia are expected to have adverse maternal outcomes at any time before discharge. Rules of thumb for fitting multivariate models suggest about 10 events for every variable are required to reduce issues with overfitting, and we will work within this constraint [24–26]. We initially planned to examine 10 predictor variables and hence planned to recruit 500 women. However, the event rate was lower than predicted, so we revised our plan to recruit sufficient women to obtain 100 events. Subsequent to the inclusion of delivery before 34 weeks as a component of the composite outcome, we revised our plan to include 22 candidate predictor variables, which was approved by the independent study Committees.

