#### Model development, apparent performance assessment and internal validation

The predictors of adverse maternal outcomes will be identified to develop and externally validate a simple, interpretable and clinically applicable prediction model with face validity. We will use a transparent process that implements appropriate statistical methods and adheres to current methodological recommendations.

A backwards selection procedure will be used to decide which of the candidate predictor variables should be included in the final prediction model (with *p* < 0.15 taken conservatively to warrant inclusion). Continuous variables will be kept as continuous in the model (rather than dichotomising), to avoid a loss of power [27, 28]. Non-linear trends will also be considered using the multivariable fractional polynomial procedure [29, 30], which uses multivariable models to eliminate weaker predictors and identify transformations of continuous predictors that best predict outcome. Large amounts of missing variable data are not expected, but some will inevitably occur, with not all patients providing all variables of interest. Multiple imputation will be used to impute, with 5 imputations, under a missing at random assumption, missing values so as to avoid excluding patients from the analysis [27].

For survival analysis, failure event is defined as an adverse outcome or delivery occurring before 34 weeks of gestation. We will use a flexible parametric survival model via the Royston-Parmar approach [31–33], with the cumulative baseline hazard scale modelled using restricted cubic splines. The number of knots will be chosen by visual inspection. For the binary adverse maternal outcome by discharge, a logistic regression-modelling framework will be undertaken with the logit probability of an adverse outcome being the response variable.

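### The overfitting rule counts events only; for the by-discharge logistic model it should count the smaller of women with and without the composite

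*Protocol article*

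**What the plan says.** All of this is in the protocol article. Under Sample size considerations, the starting point is that "20% of women with early-onset pre-eclampsia are expected to have adverse maternal outcomes at any time before discharge". The constraint follows: "Rules of thumb for fitting multivariate models suggest about 10 events for every variable are required to reduce issues with overfitting". The authors undertake to keep to it. The first plan was "We initially planned to examine 10 predictor variables and hence planned to recruit 500 women". Recruitment was then reset because "the event rate was lower than predicted, so we revised our plan to recruit sufficient women to obtain 100 events". Finally, once delivery before 34 weeks had joined the composite, the number of candidates rose: "we revised our plan to include 22 candidate predictor variables, which was approved by the independent study Committees". No new count of events, and no count of women without the outcome, accompanies the 22.

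Outcome measures and Table 3 make delivery before 34 weeks a component of the maternal composite. Statistical analysis names two models under one common framework: a survival model up to 34 weeks and a logistic model by discharge. On the second, the model development section says: "For the binary adverse maternal outcome by discharge, a logistic regression-modelling framework will be undertaken".

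**The concern.** Logistic regression treats the two outcome groups symmetrically: swapping the labels changes only the signs of the coefficients. What limits the number of predictors is therefore the smaller group. When 20% of women were expected to have the outcome, that group was the events, and counting events was right.

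The wider composite may reverse this. All women enter between 20+0 and 33+6 weeks, so all are exposed to the new component. A non-event is now a woman with no complication who is still undelivered at 34 weeks. Once more than half the cohort has the composite, each further delivery raises the event count and shrinks the limiting group. The article's rule sees only the first effect.

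The stated constraint could thus be met on paper while the logistic model has too few women in its smaller group. Predicted risks would be too extreme before correction, and backward selection would be less stable.

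**Working it through.** **1. The plan's own figure.** N = predictors × 10 ÷ event rate = 10 × 10 ÷ 0.20 = 500. This reproduces the stated 500 women and 100 events.

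**2. The requirement for 22 candidates.** Table 2 lists 22 maternal candidates: 11 continuous, 8 yes/no and 3 with several categories. At 10 per candidate, 22 × 10 = 220 women are needed in the limiting group.

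**3. Assumed cohort sizes.** The final N is not given. I read the revised target as 100 events on the composite before delivery was added, because the article gives the steps in that order. At rates of 20%, 15% and 10%, N = 100/0.20 = 500, 100/0.15 ≈ 667 and 100/0.10 = 1000. The 15% and 10% are assumptions. As the rate turned out below 20%, 500 is a lower bound on this reading.

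**4. When the rule fails on non-events.** Let p be the proportion with the composite. There are at least 220 events when p ≥ 220/N, and fewer than 220 non-events when p > 1 − 220/N.

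| N | Event rule met from p = | Non-events below 220 when p exceeds |
|---|---|---|
| 500 | 220/500 = 44% | 1 − 220/500 = 56% |
| 667 | 220/667 = 33% | 1 − 220/667 = 67% |
| 1000 | 220/1000 = 22% | 1 − 220/1000 = 78% |

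**5. Counts per candidate at p = 80%.** Events are 0.80N/22 and non-events 0.20N/22.

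| N | Events per candidate | Non-events per candidate |
|---|---|---|
| 500 | 400/22 = 18.2 | 100/22 = 4.5 |
| 667 | 533.6/22 = 24.3 | 133.4/22 = 6.1 |
| 1000 | 800/22 = 36.4 | 200/22 = 9.1 |

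**6. Effect on calibration, N held fixed.** The simulation used 22 independent standard normal predictors, of which 8 had a log odds ratio of 0.30 and 14 had none. Backward elimination kept terms at p < 0.15. The calibration slope was taken in 20,000 new patients, before any shrinkage. The figures are medians, and repeat runs differ by a few hundredths.

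| N | Slope at 50% with composite | Slope at 80% |
|---|---|---|
| 500 | about 0.77 | about 0.66 |
| 667 | about 0.83 | about 0.76 |
| 1000 | about 0.88 | about 0.84 |

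At 90%, the slopes are about 0.53 at N = 500 and 0.75 at N = 1000.

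**The case against.** **The proportion is not given.** A reader might infer that non-events are in fact the limiting group. The documents do not support that: no share of women delivering before 34 weeks is stated. Even above 50%, 10 non-events per candidate remain up to the thresholds in the second column of limits above. This stands, and the point is conditional for that reason.

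**The wider composite usually helps the logistic model too.** A reader might infer that widening the composite supports fewer candidates, or that only the survival model gains. Over much of the range neither is true. Against the 100 events first planned, the smaller group falls below 100 only above 1 − 100/500 = 80%, 1 − 100/667 = 85% or 1 − 100/1000 = 90%. At N = 500, simulated slopes are 0.68 at 20%, 0.78 at 44% and about 0.66 at 80%, so 80% is about as bad as 20%, and the middle is better.

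**Alarming slopes are easy to produce.** Holding events at exactly 220 gives slopes near 0.51 at 80% and 0.30 at 90%. Those cohorts have only 220/0.80 = 275 and 220/0.90 ≈ 244 women, whereas the section implies more than 500. Such figures mix group imbalance with a cohort the plan does not describe.

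**There are other safeguards.** The plan repeats selection in 500 bootstrap datasets, shrinks the final models by the optimism-adjusted slope, and validates externally in cohorts of 634 and 216 women. These are real. Uniform shrinkage corrects the average slope, but it neither restores information nor stabilises which predictors are selected. External validation would reveal a poor model, not prevent one.

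**The article is condensed.** The expected proportion and final N may stand in the full protocol or analysis plan, so their absence is not the complaint. The rule itself is stated in the article, and it counts one group only.

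**Conclusion.** The point holds as a conditional one, for the logistic model only. The rule as written is satisfied by events alone, so it cannot protect the by-discharge model if most women have the composite. For the survival model, counting events remains the usual basis.

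The size depends on two quantities that are not in the article. If the composite proportion is at or below 56% (N = 500), 67% (N = 667) or 78% (N = 1000), and the event rule is met, the smaller group also reaches 220 and nothing is lost. At 80%, the pre-shrinkage slope is lower than at 50% by about 0.11, 0.07 and 0.04 at those sizes. At 90% the loss is clearly larger. These slopes rest on assumed effect sizes and independent predictors, so they show direction and rough scale only.

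The 220 is itself a minimum. With categorical predictors entered as factors, Table 2 gives 11 + 8 + 2 + 2 + 4 = 27 parameters even before any fractional polynomial terms.

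**What to change.** In Sample size considerations, state the constraint separately for each model:

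- **Survival model:** keep about 10 events per candidate, counting events up to 34 weeks.
- **Logistic model:** require about 10 per candidate in the smaller of the groups with and without the composite, which is 220 for 22 candidates.

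Count both groups before any predictor-outcome analysis. If the smaller is below 220, do one of two things. Either cut the logistic candidate list to that count divided by 10, choosing on prior grounds without looking at outcome associations, or fit the model by penalised estimation. The article describes no ranking of candidates, so the basis for any cut must be written down first. Report both counts per candidate.

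The cost is a sentence or two and a small table. No extra patients are needed. The downside is that the logistic model may start from fewer than 22 candidates.

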### Statistical analysis

We will develop two prediction models: a survival model for adverse maternal outcomes at various time points from diagnosis up to 34 weeks of gestation, including by 48 h after admission, and a logistic model for adverse maternal outcomes by discharge. These will both be developed using a general methodological and statistical framework as outlined below.

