## Background

Pre-eclampsia is a multisystem disorder in pregnancy associated with hypertension and proteinuria [1–3] and occurs before 34 weeks in 1% of women, so called early-onset pre-eclampsia [4, 5]. In the UK, hypertensive disease in pregnancy remains a leading cause of direct maternal deaths and contributes to about 20% of all stillbirths [6].

With an increased risk of maternal complications and 20-fold higher maternal mortality, early-onset pre-eclampsia is considered to be pathophysiologically different from the late-onset disease [7–9]. The only known cure is delivery of the baby and placenta. However, fetal and neonatal benefits from delaying the pregnancy need to be balanced against the risk of multisystem dysfunction in the mother.

Although the proportion of women with early-onset pre-eclampsia is only 1% of all pregnancies, the complexity of the treatment gives rise to large health care costs [4, 5]. Women are often admitted to tertiary care, and with a third experiencing complications, a stay in an intensive care facility may become necessary [10]. Infants also have longer stays in intensive care facilities for management of complications such as lifelong handicaps arising as a result of prematurity.

One of the key recommendations in the last CEMACH (Confidential Enquiries into Maternal and Child Health) (now known as Centre for Maternal and Child Enquiries (CMACE)) report is the need to adopt an early warning system to help in the timely recognition, referral and treatment of women who have or are developing critical conditions [6]. Early identification of mothers with early-onset pre-eclampsia at risk of complications, and their risks for these at various time points after diagnosis, will allow clinicians to make decisions on commencing interventions such as administration of steroids and, if needed, in utero transfer to a tertiary unit. In mothers considered to be of low risk, they can be monitored as an outpatient, and delivery may be delayed to lower the risk of perinatal complications from prematurity.

We aim to develop prediction models to quantify the overall risk of adverse maternal outcomes in women with early-onset pre-eclampsia and at various time points after diagnosis.

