### Objectives

The primary objectives are to develop and internally validate a prediction model in women admitted with early-onset pre-eclampsia from 20 weeks and 0 day to 33 weeks and 6 days of gestation, for assessment of the risk of adverse maternal outcomes at 48 h and by discharge. The 48 h of time interval was chosen to reflect the time recommended for delivery after administration of steroids to lower risks of respiratory distress in newborns. This time period is also considered to be the optimal duration to make decisions on timing and place of delivery and consider in utero transfer to a tertiary care unit if needed. The model will be externally validated in two independent datasets of patients with a diagnosis of early-onset pre-eclampsia. Our secondary objective is to assess the risk of adverse fetal and neonatal outcomes at birth and at any time until discharge.

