### Study design and conduct

PREP is a prospective, multicentre, observational cohort study involving secondary and tertiary care obstetric units in England and Wales. All consecutive women with a suspected or confirmed diagnosis of pre-eclampsia before 34 weeks of gestation will be approached to take part in the study by research midwives and clinicians in antenatal clinics, wards, day assessment units and delivery suites. Clinicians managing the women will be requested to complete the Clinicians Management Plan at baseline to assess the reasons for planned management. The predictors evaluated in the PREP prediction model are routinely performed as part of standard clinical practice in women admitted with early-onset pre-eclampsia. The PREP study does not influence the management of these patients.

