### Exclusion criteria

Women will be excluded if any of the outcomes (including recurrent eclamptic seizures) occurs prior to testing or if informed consent could not be obtained on time or if the mother does not have a good understanding of spoken and written English and a translator is unavailable.

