### Candidate variables for inclusion in the model

Candidate predictor variables will be obtained from patient demographic characteristics and from clinical assessment including clinical history, examination and investigations. The predictors will be clearly defined and standardised to ensure reproducibility and enhance generalisability and application of study results to practice. Data will also be collected on any interventions applied between recruitment and outcome onset that may modify the outcome.

We will choose the candidate predictors a priori to be considered in the prediction model, based on the most promising predictor variables as identified with our previous systematic review [17–22]. The full list of variables to be evaluated for prediction of maternal and fetal outcomes is provided in Table 2.

**Table 2 Tab2:** List of candidate predictor variables to be evaluated in the PREP study

Maternal characteristics Maternal age at diagnosis (years) Gestational age at diagnosis (weeks) Number of fetuses in pregnancy at time of consent (1, 2, 3)
History Summary score for medical history—1 point for each of the following: pre-existing hypertension, renal disease, diabetes mellitus, autoimmune disease, previous history of pre-eclampsia (0, 1, 2 or more)
Symptoms Headache and/or visual disturbance (yes/no) Epigastric pain, nausea and/or vomiting (yes/no) Chest pain and dyspnoea (yes/no)
Bedside examination and tests Systolic blood pressure (mmHg, highest measurement over 6 h) Diastolic blood pressure (mmHg, highest measurement over 6 h) Clonus (yes/no) Exaggerated tendon reflexes (yes/no) Abnormal oxygen saturation (<95% on air) (yes/no) Urine dipstick (0, 1+, 2+, 3+, 4+ or more)
Laboratory tests Haemoglobin (g/L) Platelet count (× 10^9^/L) ALT (IU/L) Serum uric acid (μmol/L) Serum urea (mmol/L) Serum creatinine (μmol/L) Urine protein-creatinine ratio (PCR) (mg/mmol)
Management at baseline Administration of oral and/or parenteral anti-hypertensives (ongoing or commenced within 1 day of diagnosis) (yes/no) Administration of magnesium sulphate (commenced before or within 1 day of diagnosis) (yes/no)
Additional factors for fetal model only Uterine artery Doppler (normal/abnormal) Liquor volume (normal/abnormal) CTG findings (normal/abnormal) Estimated fetal weight <10th centile (yes/no)

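### The survival model is given two time origins and eligibility a third; to the extent that testing follows the clock start, the 48-h risk is understated

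*Protocol article*

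**What the plan says.** The Statistical analysis section describes the survival model as giving maternal risk "at various time points from diagnosis up to 34 weeks of gestation, including by 48 h after admission". The general time points run from diagnosis, but the 48-h point runs from admission. Other sections do not settle it. The Background states the aim as risk "at various time points after diagnosis". The Objectives, written for women who have been admitted, promise a model "for assessment of the risk of adverse maternal outcomes at 48 h and by discharge" and name no starting point.

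The Exclusion criteria use a third moment: "Women will be excluded if any of the outcomes (including recurrent eclamptic seizures) occurs prior to testing". Table 3 lists delivery before 34 weeks among the maternal outcomes and the model-development section makes it part of the failure event. Read together, a delivery before testing excludes the woman as well.

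Under Study design and conduct, women are approached "in antenatal clinics, wards, day assessment units and delivery suites", so diagnosis, admission and testing need not happen together. In Table 2, blood pressure is the highest value over a 6-h window, and antihypertensives and magnesium sulphate count as baseline predictors if begun up to 1 day after diagnosis. No section says that the three moments coincide, that the clock starts at testing, or that women join the risk set late.

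**The concern.** A survival model has one time zero, and the absolute risk at 48 h depends on where it lies. Suppose the clock starts at diagnosis and a woman is analysed only if she reaches testing without an outcome. She then cannot fail between the two moments, yet those hours count as time at risk. The fitted hazard is too low at the start of follow-up, which is where the 48-h risk is read.

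The treatment predictors raise a related problem. With the clock at diagnosis, they may be recorded up to 24 h into the 48-h window that they help to predict. A woman who fails at 6 h has had only 6 of those 24 h in which to be classed as treated. Treatment status can therefore depend partly on staying event-free, which affects coefficients as well as the baseline hazard.

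The 48-h risk is a primary objective. The Objectives tie it to the timing and place of delivery and to transfer, and the Background suggests that women judged low risk could be monitored as outpatients. A risk that is too low errs towards false reassurance. The bootstrap would not reveal it, because it resamples the same women on the same clock. In PETRA and PIERS, a different time origin could be mistaken for miscalibration.

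**Working it through.** **Figures in the plan.** The article gives no 48-h risk and no interval from diagnosis or admission to testing, so there is no figure on this point to reproduce. The nearest number is the expected 20% event rate by discharge in the sample size section. It gives 10 predictors × 10 events ÷ 0.20 = 500 women, as stated, and this point does not affect it. That 20% refers to discharge and to the composite before delivery was added. The 20% used below is a separate assumption about 48 h.

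**Set-up.** Let S(t) be event-free survival from the clock start, and let testing occur L hours later. Three quantities must be kept apart:

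- 48-h risk from the clock start in all women: 1 − S(48)
- 48-h risk from testing in women who reach it: 1 − S(48+L)/S(L)
- what the selected cohort yields if the lag counts as time at risk: 1 − S(48)/S(L)

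**Constant hazard.** With a true 48-h risk R, the hourly hazard is h = −ln(1 − R)/48. The first two quantities both equal R, and the third is 1 − (1 − R)^((48 − L)/48). For R = 0.20, h = 0.2231/48 = 0.00465 per hour. With L = 12 the estimate is 1 − exp(−0.00465 × 36) = 15.4%.

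| Assumed true 48-h risk | L = 0 | 2 h | 6 h | 12 h | 24 h |
|---|---|---|---|---|---|
| 10% | 10.0% | 9.6% | 8.8% | 7.6% | 5.1% |
| 20% | 20.0% | 19.3% | 17.7% | 15.4% | 10.6% |
| 40% | 40.0% | 38.7% | 36.0% | 31.8% | 22.5% |

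Each row applies one lag to every woman. If half had no lag and half had 12 h, the 20% row would give (20.0 + 15.4)/2 = 17.7%.

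**Other hazard shapes.** Weibull hazards with 1 − S(48) = 20%:

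| Hazard | Quantity | L = 6 h | 12 h | 24 h |
|---|---|---|---|---|
| Falling (shape 0.6) | cohort estimate | 14.7% | 11.8% | 7.3% |
| Falling (shape 0.6) | true 48-h risk from testing | 16.1% | 14.6% | 12.8% |
| Rising (shape 1.4) | cohort estimate | 19.0% | 17.4% | 12.9% |
| Rising (shape 1.4) | true 48-h risk from testing | 22.2% | 23.9% | 26.6% |

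In every case with a positive lag, the cohort estimate is below both the 20% from the clock start and the 48-h risk from testing. The direction therefore does not rest on the constant hazard; the size does rest on the assumed lag and risk.

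**Treatment predictors.** The 1-day window covers up to 24 of the 48 h, that is, half. The article gives no treatment rates or start times, so the effect on the coefficients cannot be quantified.

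**The case against.** The strongest reply is that loose wording is not a demonstrated bias. Diagnosis is itself made by testing: Table 1 requires repeated blood pressure readings and a urine result, and for some categories liver enzymes or platelets, which overlap with the Table 2 predictors. The Exclusion criteria do not define testing, and for some women it may coincide with diagnosis. This stands. The bias is zero where the two coincide, and the article gives no lag.

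The direction also depends on which origin is used. For a woman tested in a clinic and admitted later, a clock from admission starts after testing and contains no guaranteed event-free interval. Any event between testing and admission would instead fall before time zero. This stands too.

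A reader might infer from the recruitment settings that some women have no admission time at all. The article does not support that: the Objectives describe women who are admitted, and being approached in a clinic does not show that admission never followed. A reader might also lean on the predictor dated otherwise, "Number of fetuses in pregnancy at time of consent", but that has little bearing on a 48-h clock. The treatment window is the relevant evidence.

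Finally, the derivation of time zero could be left to an analysis plan that is not shown. That would answer silence. Here the article names an origin for a primary objective, names it two ways in one sentence, and sets eligibility by a third.

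**Conclusion.** The time origin is stated inconsistently for a primary objective and should be settled before the model is fitted. If the clock starts before testing and delayed entry is not used, the 48-h risk is understated to the extent of the lag. Treatment predictors recorded after time zero can also be conditioned on surviving to receive them.

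A reader might infer that the 48-h risk is understated as a matter of fact, perhaps by nearly half as in the 24-h column. The article does not support that, because it gives neither the lag nor the 48-h risk. The figures of 17.7%, 15.4% and 10.6% for a true 20% are illustrations that assume a constant hazard and the same lag of 6, 12 or 24 h in every woman. At lag 0 there is no bias.

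**What to change.** Name one time zero: the date-time of the baseline assessment, which the Exclusion criteria call testing. Use it for eligibility, survival time and the 48-h prediction. Count as predictors only values recorded at or before it, including antihypertensive and magnesium sulphate use. This changes how data are classified, not how women are treated.

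Alternatively, keep diagnosis as the time scale and fit the model with delayed entry at testing. The 48-h risk for a woman assessed L hours after diagnosis is then read as 1 − S(L+48)/S(L).

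Apply the same origin in PETRA and PIERS where their dates and times allow. Where they do not, report the difference in origin as a limit on the calibration results. The article does not show which date-times those datasets hold, and it promises external validation only so far as it is feasible.

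The cost is one derived time variable and a restated treatment-predictor window in Table 2, with the Objectives, Exclusion criteria and Statistical analysis sections worded to match. Applying the exclusion rule already requires knowing whether an outcome came before testing.
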